#### Data management

The case report form (CRF) will be used to record details at all stages of the study. CRF data will be entered at participating sites by trial staff onto an online database developed and managed by the Sheffield Clinical Trials Research Unit. Data will be stored in line with standard operating procedures. In order to help ensure good data quality, validation checks will be applied at point of entry, and comprehensive post-entry validation reports will be run regularly to generate discrepancies for site staff to investigate. Additionally, a sample of paper CRF records will be verified against the database data to identify any data entry issues.

#### Site monitoring

Site monitoring will be completed before, during and after the trial to monitor trial data quality. For example, confirmation of informed consent; source data verification (review of paper CRFs against source data); data entry verification (review of database records against paper CRFs); data storage and data transfer procedures; local quality control checks and procedures. Entries on CRFs will be verified by inspection against the source data. A sample of CRFs (at least 10 %) will be checked on a regular basis for verification of all entries made. In addition, the subsequent capture of the data on the trial database will be checked. Where corrections are required these will carry a full audit trail and justification.

#### Publication and dissemination policy

We will disseminate findings in peer-reviewed scientific journals and clinical and academic conferences, both national and international. A final report and monograph will be produced for the funder (National Institute for Health Research Health Technology Assessment). We will ensure regular dissemination to interested parties via the study website or mailing lists. A lay summary of findings for participants, service users and carers that is accessible to stroke survivors will be produced in consultation with the PPI group. An executive summary will be prepared for the Trusts where the research was conducted.

#### User and public involvement

A Public and Patient Involvement group has been formed for the study and will have input at the planning, conduct, analysis and dissemination stages of the study. A plain English summary of study progress will be provided to the group every 6 months and they will meet at regular intervals throughout the study. Information materials for participants will be developed in consultation with the group to ensure they are appropriate and accessible. Involvement will also include advice on considerations of how best to deliver the intervention to the stroke population, from the service users’ perspective; contributing to ideas on recruitment strategies. This group will also advise on the dissemination materials.

#### Trial management

Three committees have been established to govern the conduct of the study: the Trial Steering Committee (TSC), Data Monitoring and Ethics Committee (DMEC) and the Trial Management Group (TMG). The TSC will consist of an independent chair with clinical and research expertise in the topic area and three other topic experts. The TSC will meet at least every 6 months to supervise the overall conduct of the trial. The DMEC will consist of an independent chair with clinical and research expertise in the topic area, and two other topic experts, plus an independent medical statistician. The role of the DMEC is to review serious adverse events thought to be treatment-related and look at outcome data regularly during data collection. They will meet at least annually.

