As part of the feasibility analysis, the effect size for the 6-month PHQ-9 outcome and the difference in mean scores (and associated 95 % confidence intervals [62]) between groups will be estimated. A marginal or random effects model will be used to allow for any clustering by therapist, with baseline PHQ-9 as a covariate to check that the likely effect is within a clinically relevant range, and this will be used as confirmation that it is worth progressing with the definitive trial. The accuracy of the cut-off of the VAMS Sad in comparison with the PHQ-9 will also be checked. This information along with the acceptability of the study design and protocol to patients and carers; the safety of the intervention; patient recruitment and consent/retention rates will enable us to determine whether or not the definitive RCT is feasible.

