#### Anticipated risks and benefits

This study is not an investigation of a medicinal product and entails no invasive procedures. The benefits of BA suggested by the CALM trial include improved mood [33]. No participants will have any existing treatments withdrawn. The intervention is low risk to the trial participants however, and stopping on grounds of patient safety is not anticipated. As this is a feasibility trial, it will not stop early for efficacy. The study may be stopped as a whole because of safety concerns or issues with study conduct at the discretion of the sponsor. There are no formal statistical criteria for stopping the trial early. Decisions to stop the trial early on grounds of safety or futility will be made by the Trial Steering Committee (TSC) on the basis of advice from the Data Monitoring and Ethics Committee (DMEC).

There is a risk that participants may experience some distress from being asked about their mood, but all researchers and therapists will be trained to deal with these situations. If at any point during the baseline assessment, intervention or outcome assessment the researcher or therapist is concerned about a participant, for example, severe distress or reporting feeling suicidal, then the necessary referrals will be made.

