#### Suicide and suicidal intentions

The risks of suicide are inherent in the nature of the condition under scrutiny (depression), and for the purposes of this study are classed as adverse events. We will follow good clinical practice in monitoring for suicide risk during all encounters with trial participants. Where any risk to patients due to expressed thoughts of suicide is encountered, we will follow local suicide protocols for each participating site.

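### The DMEC's stated event review is filtered on relatedness to treatment, so it gives no by-arm comparison of serious adverse events

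*Protocol article*

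**What the plan says.** All references are to the protocol article.

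- *Trial management* gives the DMEC two tasks. One is to "review serious adverse events thought to be treatment-related"; the other is a regular look at the outcome data as they are collected.
- *Anticipated risks and benefits* says that there are no formal statistical stopping criteria. The Trial Steering Committee (TSC) decides on stopping early for safety or futility "on the basis of advice from the Data Monitoring and Ethics Committee (DMEC").
- *Data analysis* lists "the safety of the intervention" among the inputs to the judgement on whether a definitive trial is feasible.
- *Suicide and suicidal intentions* states: "The risks of suicide are inherent in the nature of the condition under scrutiny (depression"). In this trial it counts them as adverse events. It asks for "monitoring for suicide risk during all encounters with trial participants" and adds that, where a risk is found, "we will follow local suicide protocols for each participating site". It names no route to the DMEC.
- *Control arm—usual care* says that these participants do not see the trial therapist. *Intervention arm—behavioural activation therapy* allows up to 15 sessions over 4 months, with about 10 expected.
- *Randomisation and blinding* says that participants and therapists know the allocation. The 6-month assessor is blinded.

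**The concern.** A committee that advises on safety without a numerical stopping rule works by judgement, and its main tool is a comparison of events between the arms. A filter on perceived relatedness takes that tool away. It passes only events that someone has already linked to the intervention, and in this design such events can come from essentially one arm. An excess of serious events under BA that nobody had attributed to BA case by case would not be visible. Nor could the committee tell whether a few attributed events exceeded the background level in depressed stroke survivors.

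Suicide-related events deserve separate mention. They are described as part of the condition, and that description makes a judgement of not treatment-related more likely. That judgement is the one that keeps an event from the DMEC.

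**Working it through.** **Inputs.** Recruitment target 72, from 60 evaluable with 15% attrition (*Sample size calculation*); equal allocation (*Randomisation and blinding*). The article gives no rate of serious adverse events, so the rates below are assumptions.

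**Step 1: the plan's own figure.** 60 / (1 − 0.15) = 70.6, which rounds up to 71. The stated 72 is the next even number and also equals 3 centres × 12 months × 2 per month. It reproduces, and each arm has about 72 / 2 = 36 participants.

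**Step 2: which events pass the filter.** An event must be both serious and thought to be treatment-related.

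| | BA arm (about 36) | Usual-care arm (about 36) |
|---|---|---|
| Serious, thought related | reaches the DMEC | essentially cannot arise, as there is no exposure to BA |
| Serious, not thought related | does not reach the DMEC under the stated remit | does not reach the DMEC under the stated remit |

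Whatever the event rate, the usual-care count available for comparison is essentially zero.

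**Step 3: how much is withheld.** With a per-patient 6-month risk p of at least one serious event, the expected number of usual-care participants with an event is 36p. The chance of at least one is 1 − (1 − p)^36.

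| Assumed p | Expected, 36p | Chance of at least one |
|---|---|---|
| 2% | 0.7 | 52% |
| 5% | 1.8 | 84% |
| 10% | 3.6 | 98% |
| 20% | 7.2 | above 99% |

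These figures show what the filter removes. They do not estimate the trial's event rate.

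**Step 4: does the second DMEC task fill the gap?** *Patient-centred outcomes* lists mood, leisure, daily living, carer strain, EQ5D and resource use at 6 months. None is an adverse-event measure. The resource-use questionnaire may show some care contacts, but a participant who died would have no 6-month assessment.

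**Step 5: suicide-related events.** The suicide section classes these risks as adverse events and says nothing about seriousness or relatedness. An event judged serious and related would reach the DMEC; one judged part of the depression would not. The text permits both outcomes.

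**The case against.** The strongest reply is that the article condenses a fuller protocol. Definitions of seriousness, the assessment of causality, reporting routes and the DMEC charter usually sit elsewhere, and one sentence on the DMEC's role need not list everything that it receives. The article does not say who judges relatedness. The sponsor may also stop the study over safety concerns, the TSC meets at least every 6 months, and nothing says that either is denied a full listing. The intervention is described as low risk, and with about 36 per arm any comparison of events would be imprecise.

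Much of this stands, and it limits the severity. It does not remove the point, because the article states a filter and does not merely leave the matter open. An unseen charter could widen the remit, but the stated remit would then need correcting.

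A reader might infer three stronger things that the document does not support:

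- **That the DMEC sees nothing except related serious events.** The same sentence gives it outcome data, which may be shown by arm.
- **That suicide events are excluded from its review.** The suicide section calls them neither non-serious nor unrelated. Classing them as adverse events can equally mean that they must be captured, and monitoring applies at encounters with participants in both arms.
- **That a biased crude comparison of events is planned.** No such comparison is described. BA participants do have more contacts at which an event can be noted, but that is a caution for reading a listing and not a separate error.

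**Conclusion.** The point holds in a limited form. As worded, the DMEC's event review gives it no by-arm comparison of serious adverse events: essentially none of the events among about 36 usual-care participants can meet the filter. This fits poorly with the TSC's reliance on DMEC advice and with the use of safety in the progression decision. That suicide-related events may fail to reach the DMEC is a possible consequence of the wording and depends on how relatedness is judged.

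The conclusion assumes that treatment-related means related to BA, and that the one-sentence remit describes what the DMEC is given. If usual care also counted as treatment, a few more events might pass, but they would still be pre-attributed events and not a full comparison. The size in events is unknown, because the article gives no rate. The change should be made, though nothing here shows that a safety problem would in fact have been missed.

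**What to change.** Reconcile *Trial management*, *Anticipated risks and benefits* and *Suicide and suicidal intentions* so that the DMEC receives all serious adverse events and all suicide or self-harm events, by arm, whatever their attributed relatedness. Relatedness can stay as a column in the listing but should not decide what is listed.

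Mark in the listing which events came to light at a therapy visit. BA participants have up to 15 such visits and usual-care participants have none, so the committee needs to see how each event was found before it compares the arms.

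The cost is protocol wording and a DMEC report template, with no new visits or data collection. The one downside is a slightly longer listing for the committee to read.

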## Discussion

This pilot trial is designed to assess the feasibility of a definitive multicentre RCT to evaluate the clinical and cost-effectiveness of BA for treating post-stroke depression. Ethical approval was obtained on 29 January 2015. Recruitment to BEADS started in May 2015 and is planned to run until the end of April 2016.

## Abbreviations

BA, behavioural activation; BEADS, Behavioural Activation Therapy for Depression after Stroke; CALM, Communication and Low Mood; CBT, cognitive behavioural therapy; CRF, case report form; CST, Consent Support Tool; CTRU, Clinical Trials Research Unit; DMEC, Data Monitoring and Ethics Committee; IAPT, Improving Access to Psychological Therapies; PHQ-9, Patient Health Questionnaire-9; RCT, randomised controlled trial; TSC, Trial Steering Committee; VAMS, Visual Analog Mood Scales
